#### Discontinuation criteria

(1) serious adverse reactions have occurred during the study;(2) subjects develop serious complications or other serious diseases during the study, and emergency measures are needed; and(3) the subject is unable to continue the study for other reasons.

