### Sample size calculation

The data statistician will carefully compute the appropriate sample size for each group based on the difference in postintervention HAMD scores between the two groups. According to our unpublished pilot study, the HAMD score (mean ± standard deviation) in the standard care group was 16.5 ± 4.51, and the HAMD score in the integrative medicine group was 14.5 ± 3.40. The mean HAMD score in the integrative medicine group was 2 points lower than that in the standard care group. Based on a 5% false-positive error rate (α = 0.05, two-sided, the normal distribution quantile table shows that *Z*_1−α/2_ = 1.96) and 90% power (β = 0.1, the normal distribution quantile table shows that *Z*_1−β_ = 1.28), the sample size is estimated as follows:

$$\begin{array}{l} \begin{array}{l} n=\frac{{\left(Z_{1-\alpha /2}+Z_{1-\beta }\right)}^{2}\times (\sigma_{1}^{2}+\sigma_{2}^{2})}{\delta^{2}}\\ \;=\frac{{\left(1.96+1.28\right)}^{2}\times (3.40^{2}+4.51^{2})}{2^{2}}\approx 83.72 \end{array} \end{array}$$

Each group needs to include 84 participants. Assuming an ~20% dropout rate, a total of 202 participants will be enrolled in this trial.

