### Statistical analysis

Statistical analyses will be carried out by statisticians unaware of the groupings. The statistical analysis will be performed using SPSS software version 25.0. A two-sided 5% significance level will be adopted, and the corresponding 95% CI will be calculated to the greatest extent possible. A *p*-value of <0.05 will be set as the significance level.

Demographic characteristics and baseline measurements of the variables in each group will be summarized. Measurement data that conform to a normal distribution will be displayed using the mean ± SD, while the median, minimum, and maximum will describe measurement data that do not conform to a normal distribution. To assess the treatment effectiveness, outcome measurement data at baseline, after the intervention, and follow-up (i.e., 4 and 8 weeks), will be analyzed. For the qualitative data, the difference between and within groups will be tested by the chi-square or Fisher's exact test. For quantitative data, either parametric tests (Student's *t*-test) or non-parametric tests (Mann–Whitney *U*-test, Wilcoxon signed-rank test) will be used, depending on the normality of the distribution. In addition, the intention-to-treat analysis will be carried out to minimize potential attrition bias.

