### Quality control

To minimize variations during the intervention process and outcome assessment process, quality control measures will be taken. Prior to the trial, all manipulators who deliver the interventions, as well as the outcome assessors, will attend intensive training about the routine standard operating procedure (SOP) and quality assurance programs, thereby improving the homogeneity. Moreover, during the trial, experts will visit each center to inspect the quality of the outcome assessment and the standardization of intervention schemes for quality assurance.

In addition, we will try to reduce the actual dropout rate by the following strategies. First, based on training, the research team will try their best to improve the quality of treatment and physician–patient communication. Second, when participants miss a visit, the research team will call them to remind them about their visit promptly. Third, the participants will receive acupuncture, Chinese herbs, and rTMS free of charge.

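### Intention-to-treat is credited with limiting attrition bias, but the named tests need observed scores and the article does not say whether participants who discontinue are still assessed

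*Protocol article*

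**What the plan says.** For quantitative outcomes, the Statistical analysis section of the protocol article offers Student's t-test or, in its words, "non-parametric tests (Mann–Whitney *U*-test, Wilcoxon signed-rank test) will be used, depending on the normality of the distribution". It then adds: "In addition, the intention-to-treat analysis will be carried out to minimize potential attrition bias". It names no step by which an absent score would enter these tests.

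The Sample size calculation section states "Each group needs to include 84 participants" and continues "Assuming an ~20% dropout rate, a total of 202 participants will be enrolled in this trial".

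The Discontinuation criteria form one list. It includes "serious adverse reactions have occurred during the study", serious complications or illness needing emergency measures, and "the subject is unable to continue the study for other reasons". The list does not say whether a participant who meets a criterion stops treatment only or also stops being assessed.

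Three other places bear on loss of data:
- Table 1 schedules the recording of reasons for dropout.
- Data collection and management has the follow-up scales done by telephone.
- Quality control plans a reminder call after a missed visit, and states that "the participants will receive acupuncture, Chinese herbs, and rTMS free of charge".

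**The concern.** Intention-to-treat settles the group in which a participant is counted. It does not replace a missing week-4 or week-8 HAMD score. A t-test or Mann–Whitney test at a visit uses only those with a value at that visit, and a signed-rank test uses only those with both values of the pair. Unless values are imputed first, participants without a score drop out of the comparison, and the report could still carry the intention-to-treat label.

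Missing data matter most when the reason for them relates to outcome or arm. Two of the listed discontinuation reasons are harms or serious illness. Neither participants nor operators are blinded, and the arms differ greatly in treatment burden, so the rate and the reasons of loss could differ between them. What is at stake is bias in the main comparison rather than power. Part of it also cannot be repaired later, because no analysis plan can recover scores that were not collected.

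**Working it through.** **1. The plan's own figures.** Inputs from Sample size calculation: SDs 3.40 and 4.51, difference 2, quantiles 1.96 and 1.28, dropout about 20%.

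- n per arm = (1.96 + 1.28)² × (3.40² + 4.51²) / 2² = 10.4976 × 31.9001 / 4 = 83.72, so 84. Reproduced.
- 84 × 1.2 = 100.8, so 101 per arm and 202 in total. Reproduced.

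The 84 are enlarged so that enough participants remain after dropout. This implies that dropouts were expected to contribute no outcome. (Keeping 84 after a 20% loss would need 84 / 0.8 = 105 per arm, 210 in total. That is a separate matter.)

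**2. How many scores could be absent.** If the planning rate applied to the scores, 202 × 0.20 = 40.4 would be missing and 161.6 would remain, or 80.8 per arm.

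**3. Cost in power.** The root-mean-square SD is √((3.40² + 4.51²) / 2) = 3.994, and power = Φ(2 / (3.994 × √(2/n)) − 1.96).

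- n = 84: Φ(3.245 − 1.96) = 90.1%.
- n = 80.8: Φ(3.183 − 1.96) = 88.9%.

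The loss is about one percentage point, which is minor.

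**4. Possible bias.** The figures for lost participants below are assumptions; the article gives none. In one arm, completer mean minus all-randomised mean = −(fraction lost) × (how much worse the lost participants score).

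| Assumption | Error in the completer difference |
|---|---|
| 20% lost in one arm, scoring 3 points worse; the other arm's dropouts equal completers | 0.2 × 3 = 0.6 points (30% of 2) |
| The same, 5 points worse | 0.2 × 5 = 1.0 point (50% of 2) |
| 25% v 15% lost, 3 points worse in both arms | (0.25 − 0.15) × 3 = 0.3 points |
| 30% v 10% lost, 3 points worse in both arms | (0.30 − 0.10) × 3 = 0.6 points |
| 20% lost in each arm, equally worse in both | 0 |

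In the first two rows, the error flatters the integrative arm if the worse-scoring dropouts are there, and understates its effect if they are in the standard care arm. In the unequal-loss rows, it favours whichever arm loses more.

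Put another way, suppose completers show the planned 2 points and the 20% lost in each arm show 1, 0 or −2. The all-randomised difference is then 0.8 × 2 + 0.2 × 1 = 1.8, 0.8 × 2 + 0.2 × 0 = 1.6, or 0.8 × 2 + 0.2 × (−2) = 1.2.

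With 20% lost in one arm only, cancelling a 2-point difference would need dropouts 2 / 0.2 = 10 points worse than completers.

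**The case against.** The strongest reply is that much of this is silence. The article does not say that participants without a score are excluded. The same tests can be run after imputation, and the definition of the analysis set, imputation and sensitivity analyses are commonly left to an analysis plan that is not shown. That stands: a reader might infer that the plan has fixed a completer analysis, and the article does not say so.

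A reader might also infer that stopping treatment counts as leaving the study. Only the third discontinuation criterion refers to continuing in the study, and no section ends assessment at discontinuation. Telephone follow-up and reminder calls could reach some of these participants. So the list is ambiguous; it is not a rule that outcomes are lost.

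A third tempting reading is that the bias favours the integrative arm. The article does not support this either. Three added treatments could raise loss in that arm, while free provision of those same treatments could lower it, and no dropout figure is given by arm.

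The reply does not rescue the stated rationale. The article itself offers intention-to-treat as the protection against attrition bias, and nothing named beside it provides that protection. Whether outcomes are collected after discontinuation is a matter of trial conduct, and an analysis plan written later cannot settle it in retrospect.

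**Conclusion.** The point holds in a limited form. The protocol article relies on intention-to-treat to limit attrition bias, names only tests that need observed scores, plans for about 20% dropout by enlarging the sample, and leaves open whether participants who discontinue are still assessed. As written, the comparison is likely to rest on those with observed scores.

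Neither the direction nor the size of any bias follows from the document. The range of 0.6–1.0 HAMD points, 30–50% of the planned difference, rests on three assumptions: 20% loss in one arm, lost participants 3–5 points worse than completers, and dropouts in the other arm equal to completers. Equal loss with equal shifts gives no bias. The 20% is itself a planning allowance, not a stated share of missing HAMD scores. The change is worth making because it is cheap and because part of it must be in place before participants are lost.

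**What to change.** 1. **Outcome collection.** Leave the discontinuation criteria as they are. Add a sentence stating that stopping treatment is not withdrawal from the study, and that the week-4 and week-8 outcomes are still collected unless consent is withdrawn.

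2. **Analysis.** For HAMD and the other scales, replace the visit-wise tests with a repeated-measures mixed model by allocated group, with treatment, visit, treatment × visit and centre. Preferably enter baseline as a response with a mean common to both arms, so that participants with no later score stay in the model; otherwise enter it as a covariate, in which case those participants contribute nothing. The model uses data already scheduled and can be fitted in SPSS, the software the article names. It assumes that missingness is explained by the observed data, and it says little about participants who have only a baseline score, which is why item 1 comes first.

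3. **Sensitivity.** Add one analysis that shifts the missing scores in either arm, separately, over a range stated in advance, and report where the conclusion changes. The 3–5 points used above are illustrative; the investigators should justify their own range.

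The cost is some protocol wording, a few extra calls to participants who stopped treatment, and one additional analysis. The sample size need not change on account of this point.

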### Quality control

To minimize variations during the intervention process and outcome assessment process, quality control measures will be taken. Prior to the trial, all manipulators who deliver the interventions, as well as the outcome assessors, will attend intensive training about the routine standard operating procedure (SOP) and quality assurance programs, thereby improving the homogeneity. Moreover, during the trial, experts will visit each center to inspect the quality of the outcome assessment and the standardization of intervention schemes for quality assurance.

In addition, we will try to reduce the actual dropout rate by the following strategies. First, based on training, the research team will try their best to improve the quality of treatment and physician–patient communication. Second, when participants miss a visit, the research team will call them to remind them about their visit promptly. Third, the participants will receive acupuncture, Chinese herbs, and rTMS free of charge.

## Discussion

Studies have indicated that TCM (e.g., acupuncture and Chinese herbs), rehabilitation, and rTMS effectively improve the symptoms of PSD. However, it is notable that most previously published clinical studies have reported higher efficiency and fewer adverse effects when a TCM or rehabilitation therapy is added to a Western medicine control group or a control group with other therapies; however, most previous trials only added one or two TCM therapies. To date, very few clinical trials have examined the treatment of PSD that focus on the concept of integrative medicine in real-world clinical settings. Notably, in most Asian countries, especially China, aiming to optimize the therapeutic effect through closer collaborations between TCM and Western medicine, clinicians often adopt an integrative medicine approach to treat a wide range of diseases in hospitals, rather than just a sole TCM or Western medicine approach. Therefore, we designed an integrative medicine treatment protocol incorporating a total of three therapies—namely acupuncture, Chinese herbs—and rTMS for PSD. Our integrated medicine protocol incorporating the aforementioned therapies is commonly used and has promising application value for PSD in real-world clinical settings, especially in Asian hospitals, so we intend to investigate its therapeutic effect. Taken together, our study has a certain innovative quality to it.

According to TCM theory, the liver-qi stagnation pattern is the leading TCM pathogenesis of PSD. Soothing the liver and regulating qi is the treatment principle. Therefore, in terms of acupoint selection, the scalp acupoints are MS1, MS2, and MS5, which can treat mental diseases according to the expert consensus entitled *Standardized manipulations of acupuncture and moxibustion-Part 2: Scalp acupuncture* (SAC NTCoAaMo, 2021). The MS1, MS2, and MS5 are placed on the top of the head, the stimulation of which can exert local and nearby therapeutic effects. Based on *Clinical Acupuncture*, the body acupoints chosen for this study are the most commonly and normatively used by clinical practitioners. They are effective in tranquilizing the mind and relieving liver stagnation. In terms of herbal medicine, “Chai Hu Shu Gan San” has some benefits in treating depression, particularly PSD (Sun et al., 2018). In this formula, ChaiHu is the sovereign drug, and XiangFu and ChuanXiong are the minister drugs that play a role in promoting Qi and relieving depression together with ChaiHu. In addition, ChaiHu has neuroprotective effects (Li et al., 2016), XiangFu has also been found to have anti-inflammatory activity in both the peripheral and central nervous systems (Azimi et al., 2016; Farahani and Hashemi, 2016; Johari et al., 2016), and ChuanXiong is a classic herb with anti-inflammatory effects in treating cardiovascular and cerebrovascular diseases (Cao et al., 2016; Liu et al., 2016). Its conventional activity tends to be neuroprotective from a translational medicine perspective (Lin et al., 2009; Lu et al., 2014). Therefore, the prescription of Chai Hu Shu Gan San is effective in improving depression-associated neurological symptoms. rTMS is applied over the prefrontal cortex. It induces a magnetic field that results in the depolarization of underlying neurons (Wassermann and Zimmermann, 2012) and the modulation of the neural circuitry involved in emotion regulation and depressive symptoms (Barker et al., 1985, 1986; George et al., 1995; Liston et al., 2014; Salomons et al., 2014). The safety and efficacy of rTMS antidepressant therapy have been supported by multiple randomized controlled trials and published literature. These consensus recommendations, developed by the NNDC rTMS Task Group and the APA CoR Task Force on Novel Biomarkers and Treatments, provide comprehensive information for the safe and effective clinical application of rTMS in treating MDD (McClintock et al., 2018). Moreover, a previous study reported that patients with treatment-resistant depression had positive experiences and attitudes toward rTMS [Ontario Health (Quality), 2021].

However, some limitations of this study should be addressed. First, the outcome indicators used in this study are mainly patient-reported scales, which may affect the results due to the subjectivity of the patients' responses. Therefore, multiple scales are adopted simultaneously to assess the patients' depression on a multidimensional level. Second, due to limited funds, the duration of the follow-up is not long enough. Third, although the design of study groups in our study focuses more on the concept of “integrative medicine” in real-world clinical settings and the treatment protocol in these two groups is commonly used for PSD in Asian hospitals, the lack of setting a solo treatment group (e.g., acupuncture group, rTMS group) may weaken the expected findings to a certain extent.

In summary, based on this multicenter RCT with a large sample size and sound methodology, the efficacy of integrative medicine for PSD will be evaluated. Given that the integrative medicine scheme for PSD in our study integrates both TCM and Western medicine and incorporates conventional and complementary therapies, it is expected that our study will contribute to forming a standardized treatment scheme for integrative medicine for PSD in real-world clinical settings in the future.

## Ethics statement

The studies involving human participants were reviewed and approved by the Medical Ethics Committee of the Third Affiliated Hospital of Zhejiang Chinese Medical University. The patients/participants provided their written informed consent to participate in this study.

